**Fig. 2 Fig2:**

Study Schema

Consolidation duration varies by risk level for B-cell ALL participants (4 weeks standard; 8 weeks high). Consolidation duration for all T-cell ALL and T-cell LyLy participants is 8 weeks. Treatment protocols and intensity of treatment are similar for high risk B-cell ALL and T-cell participants so we include all three diagnoses under the term “high risk” when referencing duration and intensity of treatment. As such, standard risk participants receive 4 weekly sessions and high risk participants receive 8 weekly sessions. We are enrolling both standard and high risk participants to examine whether dose-response differs based on treatment duration. It is important to examine changes in child-parent stress over the full treatment cycle, and we will control for variations in number of sessions through stratified randomization and our analytic methods.

Baseline data (Time 1) will be collected after consent and before the start of the consolidation phase of treatment. Time 2 data will be collected immediately following the last study session (and no later than 7 days following last study session). Following Time 2 questionnaires, parents randomized to AME will be offered an optional parent interview (completed within 3 weeks of T2 data collection). Parents/children are encouraged to use AME and low dose play activities between clinic visits and self-reported frequency and duration of activities will be collected during each session. Data collection timelines are based on positive findings from our preliminary studies and inform our primary aims that examine mediation [33, 54]. See Fig. 2 for study schema and Table 2 for assessment timelines.

### Participants

Children and parents (or primary caregiver) will be enrolled as a dyad and must meet the following criteria to be study eligible. *Inclusion criteria*: (1) child is 3–8 years of age at time of enrollment, (2) child has diagnosis of standard or high-risk B- or T-cell ALL or T-cell lymphoblastic lymphoma (TLyLy), (3) child is currently receiving induction therapy, and (4) one parent (≥ 18 years of age) can be present for all sessions. *Exclusion criteria*: (1) child has Philadelphia positive ALL, (2) child has Cushing’s disease, (3) child takes steroid medication for asthma and/or has asthma that is not well-controlled, (4) parent does not speak English, or (5) the child has a significant cognitive impairment that might hinder participation (determination made in consultation with attending physician, oncologist, and parents).

### Sample size and power analysis

We will recruit a total sample size of 228 child/parent dyads and assume 25% attrition to retain 170 child/parent dyads (85 dyads/group) at Time 2. The primary goal of this study is to examine mechanisms via the mediation effects of the AME intervention. We will use the percentile bootstrap method to estimate the indirect/mediated effect [55]. The sample size needed for this study is primarily driven by the power needed for the mediation hypothesis in Aim 2. Simulations of the two-path mediation model in Mplus [56] show that 170 subjects are needed to have 88% power to test the total indirect effect using the Sobel approach when the effect of the independent variable (AME in this case) on the mediator is at least medium (13% of variation explained), mediator on the outcome is between small and medium (7% of variation explained), and independent variable on the outcome is small (2% of variation explained). Via simulation, the Type I error with this sample size under a model that assumes no indirect effect is also less than 0.007, which will readily accommodate the multiple comparison adjustments planned below (e.g. with 7 cytokines a conservative Bonferroni adjustment would be 0.05/7 = 0.007). A sample size of 170 will also afford 90% power to detect a medium effect size for H1.1 and H1.2 based on a two-sample t-test with a two-sided alpha level of 0.05. Fitting models that allow for repeated measures across session will result in improved power. Using the percentile bootstrap method instead of Sobel should afford the same or greater power.

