#### Missing data and multiple comparisons

We will compare all baseline variables between subjects who drop out of the study and those who do not using two-sample *t* tests, chi-square tests, or non-parametric equivalents as appropriate. MPlus software will incorporate participants who drop out before completion by using the MPLUS imputation method to perform a bias adjustment for missing data under maximum likelihood estimation and the assumption that data are missing at random. If we find that missing data are not missing at random, we will use a pattern mixture modeling approach to address; note we expect up to 25% attrition but minimal missing data on instruments (< 1%). We will adjust *p* value for multiple comparisons using the Bonferroni method for parent emotional/traumatic distress as there are two outcomes for this domain. For cytokine analyses, there are 7 cytokines of interest, so a Hochberg step-up approach will be used for these analyses.

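### Simulated Type I error below 0.007 does not cover the multiplicity adjustment: it fails when one path has its planned size, and the 88% power, inferred to be at alpha 0.05, does not carry over to the cytokine tests

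*Protocol article*

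**What the plan says.** All from the protocol article. Under Sample size and power analysis, the trial will "assume 25% attrition to retain 170 child/parent dyads (85 dyads/group) at Time 2". The size is said to be driven mainly by the Aim 2 mediation hypothesis, and simulation is reported to show that "170 subjects are needed to have 88% power to test the total indirect effect using the Sobel approach". The assumed paths explain 13% (AME to mediator), 7% (mediator to outcome) and 2% (AME to outcome) of variation. No alpha accompanies this power figure; the only one named in the section is two-sided 0.05, for the Aim 1 t-test.

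The section then states that "the Type I error with this sample size under a model that assumes no indirect effect is also less than 0.007". From this it concludes that there is ample room for the corrections for multiple testing, and it gives 0.05/7 = 0.007 for seven cytokines as an example of a conservative Bonferroni adjustment. It does not say which path was set to zero. It also says that the percentile bootstrap should have at least the power of the Sobel test.

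Under Missing data and multiple comparisons, Bonferroni is planned for the two parent-distress outcomes, and "For cytokine analyses, there are 7 cytokines of interest, so a Hochberg step-up approach will be used for these analyses". Under Main analyses, indirect effects are tested by the percentile bootstrap.

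**The concern.** An indirect effect is a product of two paths, so it is zero when either path is zero. Tests of a product are very conservative when both paths are zero and much less so when one is present. Aim 1 hypothesises that AME lowers cortisol. The null that Aim 2 chiefly has to guard against is therefore that AME moves cortisol but cortisol does not move the outcome. An error rate obtained with both paths absent says little about that case.

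A low Type I error at nominal 0.05 also does not show that power survives a stricter threshold. A reader would take the 88% to apply to the cytokine mediation tests as adjusted. If it does not, a null cytokine result could be over-read as evidence against mediation.

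**Working it through.** **Inputs** (Sample size and power analysis): n = 170, 85 per arm; variation explained 13%, 7% and 2%. Adjusted levels (Missing data and multiple comparisons): 0.05/2 = 0.025 for parent distress; 0.05/7 = 0.0071 as the smallest Hochberg step for the cytokines.

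**Model.** M = aX + e and Y = c′X + bM + e, with a = √0.13 = 0.361, b = √0.07 = 0.265, c′ = √0.02 = 0.141 as standardised coefficients. Residual variance of Y: 1 − 0.09 − 2abc′ = 0.883. The Sobel statistic is z = z_a·z_b / √(z_a² + z_b²), where z_a and z_b are the two path statistics.

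**Step 1: reproduce the 88%.** Simulated Sobel power at two-sided 0.05 is 88.3%. Other readings of variation explained give 87.4% to 92.7%. Two mediators jointly explaining 7% give 87-88%. The stated figure is therefore an alpha-0.05 figure: at 0.007 the single-mediator readings reach only 51-63%. Simulation is needed because the simple normal approximation is poor here: z_a = √(170 × 0.13/0.87) = 5.04, z_b = 3.42, z = 2.83, giving Φ(2.83 − 1.96) = 81%.

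**Step 2: power at the adjusted levels, n = 170.**

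| Two-sided level | Sobel | Joint significance | Percentile bootstrap |
|---|---|---|---|
| 0.05 | 88% | 92% | 91% |
| 0.025 | 78-79% | 86-87% | 86% |
| 0.0071 | 53% | 74-75% | 72% (run at 0.007) |

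The joint test requires both paths to be significant and serves as a proxy for the bootstrap. In closed form at 0.007 it gives Φ(3.42 − 2.70) × Φ(5.04 − 2.70) ≈ 0.76. The bootstrap power used 1,500 data sets, so the standard error of the 72% is √(0.72 × 0.28/1500) ≈ 1.2 points.

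**Step 3: Type I error at nominal 0.05.**

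| Null | Sobel | Percentile bootstrap |
|---|---|---|
| Both paths zero | 0.0001 | 0.001 |
| AME to cortisol 13%, cortisol to outcome zero | 0.033-0.034 | 0.052-0.057 |
| AME to cortisol zero, cortisol to outcome 7% | about 0.020 | 0.050 |

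A hand check of the Sobel column: |z| is always below the smaller of |z_a| and |z_b|. With both paths zero, rejection needs both to exceed 1.96, so its probability is below 0.05 × 0.05 = 0.0025. With z_a held at 5.04, rejection needs |z_b| > 1.96 × 5.04/√(5.04² − 1.96²) = 2.13, which has probability 0.033. With the 7% path alone, z_b = √(170 × 0.07/0.93) = 3.58, and the same formula requires |z_a| > 2.34, probability 0.019.

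**Step 4: how small must the lone path be?** Simulated Sobel error with only the AME-to-cortisol path present is 0.001 at 1%, 0.003 at 2%, 0.006 at 3%, 0.012 at 5%, 0.018 at 7% and 0.033 at 13%. The bound of 0.007 therefore holds up to about 3% and fails at both planned sizes.

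**Step 5: could another reading reconcile the two figures?** If the error was simulated at nominal 0.007, the Sobel bound holds under every null, but power at that level is not 88%. If two mediators each explained a further 7%, Sobel power would be 98-99% at 0.007, but over 99% at 0.05, so that reading does not give 88% either.

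**The case against.** The plan has a fair defence, and much of it stands.

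- A reader might infer that the 0.007 bound holds only if neither path exists. It also holds with one small path (Step 4). What can be said is that it fails at the planned path sizes.
- A reader might infer that power for the planned analysis falls from 88% to about 53%. That is the Sobel figure, and the trial tests with the percentile bootstrap. The protocol's remark that the bootstrap has the same or greater power is borne out; it keeps about 72-75% at 0.0071.
- A reader might infer that the true error is seven times the stated bound. Only the bootstrap with a sizeable path comes near that (0.05/0.007 ≈ 7). For Sobel, the test behind the sentence, the ratio is about 3 to 5 (0.020/0.007 and 0.034/0.007).
- The level 0.0071 is the protocol's illustration and the strictest Hochberg step, not the level every cytokine must meet. Power at that level is a lower bound for each cytokine.
- The planned adjustments are kept, and nothing in the document uses the sentence to skip them. No decision rule or family-wise error control is altered.

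None of this rescues the inference. The bound does not hold at the planned path sizes, does not transfer to the planned test, and says nothing about power at an adjusted level.

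**Conclusion.** The inference from Type I error below 0.007 to multiplicity being accommodated is wrong as written. With one path at its planned size, error at nominal 0.05 is about 0.034 or 0.020 for Sobel and about 0.05 for the bootstrap. The stated power is close to right for the parent-distress outcomes under the planned test (about 86-87% at 0.025). It is unaffected for child emotional distress, child quality of life and parent quality of life, for which no cross-outcome adjustment is named. The material shortfall is confined to H2.1: about 72-75% per cytokine at the strictest step, against a stated 88%.

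The documents do not support reading this as a general failure of Aim 2 power or as uncontrolled error.

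Assumptions: alpha 0.05 for the 88% is inferred from reproducing it, not stated; the main figures use squared standardised coefficients, and Sobel power at 0.007 ranges from 51% to 63% over the readings tried; covariates and the T1 outcome are not modelled.

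**What to change.** In Sample size and power analysis:

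1. Delete the inference that a simulated error below 0.007 accommodates the adjustments.
2. For each simulated figure, state the nominal alpha and the null, including which path is zero. Report Type I error with one path at its planned size, for each path in turn.
3. Restate power for the percentile bootstrap at 0.05, 0.025 and 0.0071, labelling the last as the strictest Hochberg step and hence a per-cytokine lower bound.
4. Keep the Hochberg and Bonferroni adjustments in full and leave the sample size unchanged.

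The cost is a rerun of an existing simulation. The downside is a less favourable stated power for the cytokine outcomes.

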### Setting

Young children (ages 3–8 years) and their parents are being recruited from three children’s hospitals. These hospitals are in metropolitan areas that serve large catchment areas. All three sites are members of the Children’s Oncology Group, and administer chemotherapy according to protocol guidelines, ensuring consistency of treatment across sites. Study conditions and data collection sessions will take place in the outpatient clinic setting.

### Recruitment and informed consent

This study has received single Institutional Review Board Approval from the Indiana University Institutional Review Board which serves a central IRB for all participating institutions. Project managers at each site recruit children/parents during a scheduled clinic visit during the induction phase of treatment. During initial approach, project managers provide initial study introduction/brochure and verify eligibility. For interested families, child/parent dyads are enrolled following written, informed parental consent for parent and child and written assent for children ≥ 7 years, following human subjects review committee requirements.

### Study condition procedures

Children/parents randomly assigned to AME or attention control receive sessions that are similar in length (30 min. AME; 20 min. ASB) and have the same timing of contact (4 weekly sessions standard risk; 8 weekly sessions high risk). In previous AME trials, the AME and ASB conditions were delivered in an in-patient setting and had an equal duration (45 min, with 30 min of music or stories) [33–36]. The current trial takes place in the outpatient clinic setting. To accommodate clinic flow and patient needs we needed to limit session duration to 30 min or less. As such, total session duration for AME sessions is 30 min total (5 min collaborative goal setting; 20 min of music-play; 5 min educational content). Total session duration for ASB is 20 min (5 min set-up; 15 min audio-storybooks – the length of one storybook). Although total session length is not equivalent, the amount of audio-visual stimulation is similar across groups, with the additional 10 min in AME attributed to assessment and educational activities that are unique to that condition. In addition to in-person sessions, participants take home a music-play or audio-storybooks kit to encourage between session use of the condition-related activities [33–37].

Both conditions are standardized (content, materials, and delivery), and all sessions are delivered by a board-certified music therapist in the outpatient clinic setting. All sessions are audio-recorded for quality assurance monitoring to ensure fidelity and prevent provider drift and/or contamination across treatment and control conditions (see Treatment Fidelity below).

#### Active music engagement (AME) intervention

The AME was designed based on the Contextual Support Model of Music Therapy (CSM-MT) [32] which is grounded in Self-Determination Theory [39], and further informed by Kazak’s Pediatric Medical Traumatic Stress Model [40]. The CSM-MT explains how music can be used to create a supportive environment by offering optimal levels of structure, autonomy support, and relationship support [38].

AME intervention sessions were designed for delivery by a board-certified music therapist who tailors music experiences to encourage active engagement in and independent use of music play as a strategy to manage emotional distress. During AME sessions, the music therapist provides children/parents repeated opportunities to experience competence, autonomy, and meaningful interactions through music play activities, which leads to active engagement and positive forms of coping. In addition, the therapist provides supportive education about ways music play can be used to manage distress and promote a sense of normalcy both during and between clinic visits.

There are three components to the AME intervention: (1) therapist-led music play activities, (2) the music play resource kit (to promote independent music play), and (3) tip sheets for parent education and support that focus on information and strategies aimed to help parents use music play to manage their child’s distress (the focus of the AME intervention) during clinic visits, and how to use music play at home. Table 1 shows the relationship of essential AME intervention content to CSM-MT theoretical principles.

**Table 1 Tab1:** Active Music Engagement Intervention Components and Theoretical Principles

Intervention Component	Theoretical Principles
Component 1: Music-Based Play Activities	1. Predictable environments provide structure that supports child *competence*. Therapist uses familiar music activities to provide structure and increase child’s ability to predict what will happen in their environment. 2. Leveled activities help ensure success and support child *competence*. Therapist tailors physical activity requirements to meet the individual needs of each child. Enables child success and engagement during periods of high or fluctuating symptom distress. 3, Opportunities to make independent decisions support child *autonomy*. Child chooses from a variety of music play activities, and each activity includes a wide range of materials. Activities include a wide range of materials and activity options so child can make choices for self and others. Therapist uses improvisational techniques to follow child-initiated changes in their music making (e.g., child changes tempo or style of playing). 4. Activities structured to support *caregiver-child interaction*. Activities are designed to structure and support reciprocal caregiver-child interactions. Therapist individualizes experiences to support increased frequency and quality of interactions.
Component 2: Music Play Resource Kit	Supports *independent use* of music play to manage distress between therapist-led sessions. Activities mirror content from therapist-led sessions. The kit includes: 1. Professional audio recording of music composed and/or arranged specifically for the AME intervention. 2. Age-appropriate musical instrument and play materials that correspond to each activity. 3. Activity cards designed to give children/caregivers information “at-a-glance” on ways they can use their kit.
Component 3: Session Planning & Caregiver Tip Sheets	1. Promotes caregiver *competence* about how children use play to cope and ways to engage their child in music play during transplant. 2. Promotes caregiver *autonomy* by empowering caregivers with skills/resources to support their child during treatment 3. Supports caregiver-child *relationships* through normalizing, music-based play activities

^*^ Table reprinted with permission in accordance with creative commons open access license ‘Attribution-Noncommercial 4.0 International’ (CC BY-NC 4.0) http://creativecommons.org/licenses/by-nc/4.0/ for the following publication: from Russ KA, Holochwost SJ, Perkins SM, et al. Cortisol as an acute stress biomarker in young hematopoietic cell transplant patients/caregivers: active music engagement protocol. *JACM*. 2020;26(5):424–434

#### Audio-storybooks (ASB) attention control condition

Trained music therapists also deliver the ASB condition, which was designed to control for attention from a provider, shared parent-child experiences, and audio-visual stimulation that comprise the non-therapeutic aspect of the AME condition. It offers parents/children opportunities to make choices and engage in an age-appropriate, non-music-based play activity. In each session, parents/children choose and listen to one of several illustrated children’s books with audio-recorded narration. In our prior work, this condition was acceptable to children and parents and did not demonstrate any significant benefits on our outcomes of interest, making it the best control condition for this trial [32–34].

### Treatment fidelity strategies

For this trial, our team developed treatment fidelity strategies based on our prior studies [57] and NIH Behavior Change consortium recommendations [58]. Specific strategies for the five specified fidelity components (design, provider training, treatment delivery, treatment receipt, and treatment enactment) are central to ensuring study rigor and reproducibility. A description of treatment fidelity strategies for this trial, including strategies to reduce risk for bias and contamination between conditions, are detailed in a separate publication [37].

### Outcome measures and data collection procedures

#### Parent (caregiver) report measures

Following informed consent, project managers at each site arrange a time for parents to complete baseline (T1) questionnaires during their first consolidation phase clinic appointment. A trained data collector administers questionnaires and remains available for questions. After completing T1 questionnaires, the project manager notifies the child/parent of their group assignment and schedules their first study condition session. Parents complete Time 2 questionnaires within 7 days of completing their last study session (session 4 for standard risk; session 8 for high risk).

The use of valid, reliable measures helps to ensure study rigor and reproducibility of results. All measures reflect careful consideration of psychometric properties, sensitivity to change, and response burden. Table 2 provides a list of measures, psychometrics, and administration schedule.

**Table 2 Tab2:** Measures

Variable(s)	Measure	# Items	Reliability Evidence	Admin. Schedule	Done By
**Antecedent Factors**					
Demographics	Family Information Form	3	N/A	T1	Parent
Prior Distress w/ Hospitalization Parent Traumatic Stress Screener	Prior Illness Experiences Scale (PIES)[59] Abbreviated PTSD checklist (PCL-S)[60]	13 6	0.78† 0.94†	T1 T1	Parent Parent
Disease and Tx Characteristics	Diagnosis and Treatment Form	2	N/A	T2	PM/ Co-I
**Mediators**					
Child Stress Parent Stress	Salivary Cortisol Salivary Cortisol	N/A N/A	N/A N/A	Pre/Post Sessions 1–4	Data Collector
**Child Outcomes**					
Child Immune Function	Immunomodulatory Cytokines (Blood)*	N/A	N/A	Pre-Sessions 1, 4, 8	Nurse/ Phleboto-mist
Child Emotional Distress	CHQ – *Mental Health Subscale*[61]	16	0.81†	T1, T2	Parent
Child Quality of Life	KINDL^R^ [62]	20	0.89†	T1, T2	Parent
**Parent Outcomes**					
Parent Emotional and Traumatic Stress Symptoms	Profile of Mood States-Short Form (POMS)[63] Impact of Events Scale-Revised (IES-R)[64]	37 22	0.99** 0.84-0.91†	T1,T2 T1, T2	Parent Parent
Parent Quality of Life	Index of Well-being[65]	9	0.93†	T1, T2	Parent

†Cronbach’s alpha; **correlation with POMS

*Blood taken during scheduled draw

